### The therapeutic digital platform

The mobile application will be built using the Progressive Web App (PWA) approach. The frontend will be developed using the React framework, while the backend will be powered by Node.js. The application will also offer offline functionality, allowing users to interact with it even without an internet connection. Regarding the patient-entered data, it will be secured using the AES protocol (Advanced Encryption Standard). AES is a widely used symmetric encryption algorithm that ensures data confidentiality through its block cipher design. It operates by dividing data into fixed-size blocks and encrypting/decrypting them using a secret key. This protocol involves multiple rounds of substitution, permutation, and mixing, making it highly secure against various cryptographic attacks.

Regarding data analysis, the medical group will have access to a Power BI dashboard designed to provide real-time visualization of their patients’ information. This dashboard will include an alert module that is developed in collaboration with the medical team. The purpose of this module is to establish thresholds and alarming associations for their patients’ data, enabling timely alerts when certain conditions are met.

The application will be divided into two sections. The first section is "Patient data collection," where patients will submit their information daily.

The patient data from will be transmitted daily and visualized by the treatment team.

The second functionality is the "Education" feature, which entails sending patients notifications regarding both group and individual sessions.

This section serves not only as an information resource but also offers a secure messaging module enabling patients to interact with their healthcare team.

As for the data collected through the "Patient Information" module, it will be sent to the treatment team on a daily basis, allowing them to regularly monitor and analyze the patient’s progress.

Access to educational tools (digital media) is available to all initial program members. These tools will be updated annually by the rehabilitation team in line with the recommendations of learned societies.

The platform also offers the possibility of organizing an individual or group remote educational session (videoconferencing modules enabling group and individual sessions), and a secure integrated caregiver-patient messaging system.

*First step: Inclusion in the therapeutic digital platform*

At the end of the TPE program, the medical team verifies eligibility for the digital platform program. A "therapeutic support" contract is signed by the program participant and the medical team, setting out the therapeutic objectives during follow-up, as well as the parameters to be collected and transmitted to the platform.

The TPE team will educate the patient in the use of the mobile application, which is based on the codes and uses of consumer applications.

*Second step: digital monitoring phase*

Every day, the patient will be invited to transmit the monitoring parameters set out in the "therapeutic support" contract.

Data will be transmitted asynchronously and securely on the monitoring platform.

*Third step: Data analysis phase*

The medical team can interact with the patient via the platform. If necessary, the patient can be called into the center by the medical team for reassessment and early consultation, in order to optimize his or her care pathway.

*Forth step: Assessment phase*

At 12 months, an assessment of knowledge retention will be carried out, as well as the incidence of major cardiovascular events.

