## Materials and methods

### Study design

This study is a controlled clinical trial. The trial has been registered at the Pan African Clinical Trial Registry (PACTR202307694422939) after enrolment of the first participant.

The results will be reported according to the CONSORT guidelines [14]. This study is approved by the Institutional Review Committee of Sahloul University Hospital (Approval No. HS12-2022). Written informed consent will be obtained from all patients who meet the inclusion criteria and are willing to participate before randomization.

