**Fig 1 pone.0300250.g001:**
[figure not shown]
The schedule of enrolment, interventions, and assessments *. *Recommended content can be displayed using various schematic formats. See SPIRIT 2013 Explanation and Elaboration for examples from protocols. **List specific timepoints in this row.

Patients will be included in the study if they: (a) are 18 years or older; (b) have a documented diagnosis of coronary heart disease including acute myocardial infarction (AMI) (Non ST and ST elevation MI), patients with unstable angina, and patients with stable angina; (c) have access to a computer, and (d) agree to participate.

The exclusion criteria include: patients who are (1) with a history of psychiatric and neurological disorders; (2) unable to speak or understand Arabic; (3) with impaired bilateral hearing, or visual impairment which limits the use of computers; (4) with contraindications or severe physical disabilities that limit patients from participation; Additional exclusion criteria will be applied if patients are not able to understand the procedure and the aims of the study after full explanation.

By using the results of a meta-analysis published in 2017 [5] for an incidence of a major cardiovascular event of 13.8% in the intervention group and 38.6% in the control group, with a power of 80% and a first-species risk α of 0.05, we found a size of 56 patients in each group.

All investigators in this study will attend rigorous training on data collection and research protocol.

Training sessions will be thorough, and detailed. The purpose of this rigorous training is to ensure that all investigators have a comprehensive understanding of the data collection methods and research protocols relevant to the study.

The research protocol encompasses the set of guidelines, procedures, and ethical standards that govern how the research study will be conducted. It includes considerations such as participant recruitment, informed consent, data handling, confidentiality, and data analysis methods.

These sessions will be held before the start of the survey to prevent measurement bias. In addition, all investigators are trained in the principles of therapeutic education.

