### Intervention group

Patients assigned to the intervention group will first receive therapeutic education. The digital platform will then enable care providers to support them remotely.

A questionnaire will be distributed to patients before they begin the TPE program, in order to assess their knowledge of the disease, their eating habits, their physical activity, etc.

The same questionnaire will be distributed again at the end of the intervention, to study the impact of the TPE program in terms of knowledge retention.

Participants assigned to the intervention group will be divided into sub-groups. Each group will receive three TPE sessions. Educational sessions will be held once every week.

TPE sessions will include theoretical presentations on the pathophysiology of coronary artery disease, its risk factors, therapeutic objectives and therapeutic management.

These sessions will also include practical workshops using video sequences, role-playing and card games, covering heart attack alert, biological and blood pressure therapeutic objectives, the Mediterranean diet, the different commercial presentations of drugs, and types of social coverage.

At the end of each session, a round-table discussion will be held on the daily life of a coronary sufferer: physical activity/stress management/smoking/returning to work.

During the last session, each patient will benefit from an individual interview during which a lipid and glycemic assessment will be requested to evaluate the impact of the TPE in the medium term.

In addition, each patient will receive leaflets in Arabic, summarizing what will be presented during the TPE sessions.

At 3 months after completion of the TPE program, the same questionnaire will be redistributed, a biological check-up will be requested, and a quality-of-life assessment will be carried out.

In a second phase, the intervention group will be monitored via a digital platform.

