### Control group

The control group will receive the usual controls at the hospital. Patients of the control group will not receive the TPE program neither a digital monitoring.

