### Outcomes

#### Primary outcome

The primary outcome of this study is the occurrence of major cardiovascular events in the year following hospital discharge for the control group, and in the year following completion of the TPE program with digital follow-up for the intervention group.

The primary outcome is based on the occurrence of acute myocardial infarction, stable angina, coronary revascularization, stroke, hospitalized heart failure, or death attributable to any cardiovascular disease [15]. Information on the primary outcome will be systematically obtained through follow-up interview at 12 months and confirmed by reviewing patients’ medical records. If a patient dies during follow-up, this information will be obtained directly from patient’s family or confirmed by physician.

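### The intervention arm's primary outcome window depends on completing TPE and follows a platform check made after randomisation; controls have neither condition

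*Protocol article*

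**What the plan says.** All references are to the Protocol article.

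- **Study design** puts consent ahead of allocation: "Written informed consent will be obtained from all patients who meet the inclusion criteria and are willing to participate before randomization".
- **Intervention group** sets the order after allocation: "Patients assigned to the intervention group will first receive therapeutic education". There are three weekly sessions, and the platform follows.
- **The therapeutic digital platform**, first step: "At the end of the TPE program, the medical team verifies eligibility for the digital platform program". The participant and the team then sign a therapeutic support contract. The section gives no eligibility criteria and does not say what happens to a patient who fails the check or does not sign.
- **Control group**: "Patients of the control group will not receive the TPE program neither a digital monitoring". Controls therefore meet neither the check nor the contract.
- **Primary outcome** starts the control year at hospital discharge. For the other arm it counts events "in the year following completion of the TPE program with digital follow-up for the intervention group".
- **Abstract, Methods** defines the primary outcome over one year from discharge and makes no distinction between arms.
- **Settings and participants**, inclusion criterion (c), requires that patients "have access to a computer". The platform section describes the tool this way: "The mobile application will be built using the Progressive Web App (PWA) approach".

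**The concern.** Randomisation makes the arms comparable at the moment of allocation. That protection holds only if the outcome is defined in the same way, from the same point, for everyone allocated. Here the control arm's clock starts at an event that every control has reached. The intervention arm's clock starts at an event that some patients may never reach, and a check and a contract stand between TPE and the platform.

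Patients who drop out of education, cannot use the tool or decline it may well be sicker or less adherent than those who continue. If they, or events before TPE ends, go uncounted in one arm only, the intervention arm looks better with no treatment effect at all. The planned chi-squared or Fisher comparison of percentages (Data analyses) has no means of correcting this. It is the primary comparison that is at stake.

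**Working it through.** **1. The plan's own figure.** Inputs from Settings and participants: 13.8% v 38.6%, power 80%, α 0.05 (taken as two-sided). The mean risk is 0.262 and the difference 0.248.

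n = [1.96√(2 × 0.262 × 0.738) + 0.8416√(0.138 × 0.862 + 0.386 × 0.614)]² / 0.248² = 48.2, so 49 per arm. The continuity correction, (n/4)[1 + √(1 + 4/(n × 0.248))]², gives 55.9, so 56. The stated 56 per arm is reproduced. The total of 112 is 2 × 56, with no allowance for loss.

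**2. Who has an outcome window?** Reading the sections together:

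| Patient | Primary outcome section | Abstract |
|---|---|---|
| Any control | Year from discharge | Year from discharge |
| Intervention, completes TPE, joins platform | Year from completion | Year from discharge |
| Intervention, does not complete TPE | No start date | Year from discharge |
| Intervention, ineligible or declines contract | Unclear: TPE done, no digital follow-up | Year from discharge |
| Intervention, event before TPE ends | Event falls outside window | Event counted |

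The two definitions agree for controls and differ for every intervention patient.

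**3. Illustration of selective loss.** The documents give no rate of loss, so f and r below are assumptions. Take no treatment effect and a true risk of 38.6% in both arms. A share f of the intervention arm goes uncounted, with r times the risk of those kept. The risk among those kept is 0.386 / (1 − f + f·r). The false-positive rate is the exact binomial rejection rate of the two-sided Pearson chi-squared test, with 56(1 − f) patients, rounded, against 56.

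| f | r | Patients kept | Risk among kept | Spurious benefit | Two-sided rejection | Favouring intervention |
|---|---|---|---|---|---|---|
| 0 | – | 56 | 38.6% | 0 | 4.8% | 2.4% |
| 10% | 1 | 50 | 38.6% | 0 | 5.0% | 2.5% |
| 10% | 1.5 | 50 | 36.8% | 1.8 points | 5.4% | 3.8% |
| 10% | 2 | 50 | 35.1% | 3.5 points | 6.5% | 5.6% |
| 20% | 1 | 45 | 38.6% | 0 | 5.1% | 2.6% |
| 20% | 1.5 | 45 | 35.1% | 3.5 points | 6.6% | 5.6% |
| 20% | 2 | 45 | 32.2% | 6.4 points | 10.3% | 9.9% |
| 30% | 2 | 39 | 29.7% | 8.9 points | 14.1% | 13.9% |

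For example, f = 20% and r = 2 gives 0.386 / (0.8 + 0.4) = 0.322.

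**4. Illustration of the later start.** Suppose a share g of first-year events falls before TPE ends, and the intervention arm is counted only among patients event-free at that point, up to 12 months from discharge. The risk is then 0.386(1 − g) / (1 − 0.386g). With g = 3/52 = 5.8% it is 37.2%, a spurious 1.4 points. With g = 10% it is 36.1% (2.5 points), and with g = 20% it is 33.5% (5.1 points). This is an upper illustration, because it counts nothing after month 12 from discharge. If a full year after completion is counted and the event rate is constant, this component disappears. It matters to the extent that events cluster early. The delay from discharge to the first session is not stated.

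**The case against.** A reader might infer that the trial will compare selected completers with all controls, so that the arms compared are not the arms randomised. The article does not support that as a statement of fact. Nowhere does it say that ineligible or non-completing patients are dropped, and it sets no analysis population, which an article may properly leave to the analysis plan. Several places point the other way. The abstract's window covers everyone from discharge, all participants are to be followed for a year, outcome information is to be collected systematically at 12 months, and reporting will follow CONSORT. The Primary outcome phrase can also be read as setting when the clock starts, not who is counted. The eligibility check may only confirm entry criteria, and the contract is described as setting objectives and parameters, not as a condition of staying in the trial.

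A second tempting inference is that screening on computer access while supplying a mobile application makes late ineligibility likely. That is conjecture. A Progressive Web App may run on a computer, and no section says that a phone is required. Only the mismatch in wording stands.

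The rates of loss and the risk ratios are also assumed, and the bias starts from zero.

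All of this limits the claim but does not remove it. The arm-specific start is written into the outcome definition. An intention-to-treat sentence in an unshown analysis plan would place a non-completer in the analysis set but give that patient no date from which to count. The abstract's definition does not settle the matter either, because it contradicts the fuller one.

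**Conclusion.** The point holds in a limited form. The article fixes an outcome window that differs by arm, ties the intervention window to completing TPE with digital follow-up, and puts an eligibility check with unstated criteria after randomisation in that arm only. This conflicts with the abstract and leaves some randomised intervention patients without a defined primary outcome, while every control has one. Where those patients have higher risk, the direction of bias is towards the intervention.

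Exclusion of these patients is a risk under one reading and not a stated rule. The documents do not give the size of any bias. Under the assumptions shown, the two-sided false-positive rate moves from 4.8% to between 5.4% and 6.5% at 10% loss and between 6.6% and 10.3% at 20% loss. It stays at about 5% if those lost carry the same risk as those kept. Because the defect lies in the primary outcome definition and is cheap to remove, it should be corrected before outcomes are assessed.

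**What to change.** 1. Rewrite the Primary outcome section with one time origin for both arms, for example randomisation, or discharge as in the abstract. Use a 12-month window that counts every event from that point, and make the abstract and the Primary outcome section agree.
2. Ascertain this outcome in all 112 randomised patients and analyse them as assigned, whatever their TPE completion, platform eligibility or contract status. Any completer analysis is supplementary.
3. Move the platform-suitability check to screening, before randomisation, in both arms, and state its criteria. Clarify whether computer access is the device requirement for the application. The Study design section says that registration followed enrolment of the first participant, so this step may come too late for some patients. For them, items 1 and 2 carry the protection.

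**Cost.** The changes are to wording, one reordered screening item, and follow-up of patients who leave the programme. The estimated effect may be smaller than among completers. To show the range, assume that a share f of the intervention arm never reaches the platform and keeps the full control risk. This is pessimistic for those who did receive TPE. The arm's risk is then (1 − f) × 13.8% + f × 38.6%.

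| f | Intervention-arm risk | Power at 56 per arm (no continuity correction) | n per arm for 80% power (continuity-corrected) |
|---|---|---|---|
| 0 | 13.8% | 86% | 56 |
| 5% | 15.0% | 81% | 63 |
| 10% | 16.3% | 76% | 71 |
| 20% | 18.8% | 64% | 91 |

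The sponsor should state the non-uptake it expects and say whether 112 still suffices.

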### Control group

The control group will receive the usual controls at the hospital. Patients of the control group will not receive the TPE program neither a digital monitoring.

### Outcomes

#### Primary outcome

The primary outcome of this study is the occurrence of major cardiovascular events in the year following hospital discharge for the control group, and in the year following completion of the TPE program with digital follow-up for the intervention group.

The primary outcome is based on the occurrence of acute myocardial infarction, stable angina, coronary revascularization, stroke, hospitalized heart failure, or death attributable to any cardiovascular disease [15]. Information on the primary outcome will be systematically obtained through follow-up interview at 12 months and confirmed by reviewing patients’ medical records. If a patient dies during follow-up, this information will be obtained directly from patient’s family or confirmed by physician.

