**Methods:**

This study is a randomized controlled trial. Patients with coronary heart disease will be recruited from one clinical site and randomly assigned into two groups: the intervention group and the control group. All participants will be followed up for a total of one year (with three-time points for data collection). Patients who are assigned to the intervention group will receive therapeutic education at first. The digital platform will then allow healthcare providers to accompany them outside the hospital walls. The primary outcome is the incidence of major cardiovascular events within one year of discharge. Main secondary outcomes include changes in health behaviors, medication adherence, and quality of life score. The digital platform is a multi-professional telemonitoring platform that allows care teams to accompany the patient outside the hospital walls. It allows the collection and transmits information from the patient’s home to the therapeutic education team. All data will be secured at a certified host. The patient application provides data on compliance, adherence to physical activity (number of steps taken per day), adequate diet (weight gain, food consumed during the meal, compliance with low-salt or salt-free diet, diabetic diet), smoking cessation, as well as medication adherence. Access to educational tools (digital media) is provided to all initial program participants. These tools will be updated annually by the rehabilitation team on the recommendations. The platform also offers the possibility of organizing an individual or group remote educational session (videoconference modules allowing group and individual sessions), a secure integrated caregiver-patient messaging system. The control group will receive the usual controls at the hospital.

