### Settings and participants

Eligible patients will be recruited from the department of cardiology of Sahloul university hospital over one month. All participants will be followed up for a total of one year (with three time-points for data collection) (Fig 1).

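### The primary outcome year starts at hospital discharge in the control arm but at completion of TPE in the intervention arm, so events in between count against the control arm only

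*Protocol article*

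**What the plan says.** Under Outcomes, Primary outcome, the article sets the event window separately by arm: "in the year following hospital discharge for the control group, and in the year following completion of the TPE program with digital follow-up". The first window is the controls' and the second is the intervention arm's.

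Other places bear on this:

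- Abstract, Methods: "The primary outcome is the incidence of major cardiovascular events within one year of discharge". There is no split by arm.
- Settings and participants: "All participants will be followed up for a total of one year". The Intervention section repeats this. Neither place names the date from which the year runs.
- Intervention group: "Each group will receive three TPE sessions", and "Educational sessions will be held once every week". The wait before the first session is not given.
- Control group: controls receive neither TPE nor digital monitoring, so they have no completion date that could match.
- The therapeutic digital platform, first step: when TPE ends, the medical team checks eligibility for the platform. This happens in the intervention arm only.

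Nowhere does the article say that events before TPE completion are counted in the intervention arm.

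**The concern.** Randomisation makes the arms comparable from the moment of allocation. That protection is lost if one arm is observed from an early, fixed date and the other from a later date that a patient reaches only by surviving and finishing a treatment component. This is the familiar immortal-time problem, here written into the primary outcome definition.

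Two things follow:

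1. Early events are counted on one side only. Patients with myocardial infarction or unstable angina are eligible. If their risk is higher soon after discharge, the rule favours the intervention even when it does nothing.
2. Some randomised intervention patients have no outcome as defined: those who die before TPE completion and those who never complete it. If digital follow-up is part of the start condition, patients who fail the eligibility check may join them.

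The primary endpoint is affected, and no analysis of the outcome as defined can restore the excluded events.

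**Working it through.** **The plan's own figure.** Inputs from Settings and participants: 13.8% v 38.6%, power 80%, α 0.05. The two-proportion formula, two-sided with continuity correction, gives 56 per group, as stated (49 without the correction). The choice of time zero does not enter this calculation.

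**Inputs for the size of the bias**

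- From the article: one-year control risk R = 0.386; 56 per arm; planned difference 38.6 − 13.8 = 24.8 points.
- Assumed: no true treatment effect; TPE completed d = 4 weeks after discharge; a share s of first-year events falling in those 4 weeks; constant hazard afterwards.

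Three weekly sessions span at least 2 weeks from first to last, so 4 weeks allows a short wait. The article states neither d nor s.

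**Formulas**

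- Risk in the first 4 weeks: sR.
- Later weekly hazard: λ = ln[(1 − sR)/(1 − R)]/48, which keeps the one-year risk at R.
- Intervention window, weeks 4 to 56:
  - early-event patients dropped: p = 1 − exp(−52λ);
  - early-event patients kept, early event uncounted: p = (1 − sR)(1 − exp(−52λ)).
- Spurious benefit: R − p.

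The second version treats an early-event patient as event-free throughout. A repeat event inside the window would count, so it is an upper value.

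**Worked case, s = 0.25**

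- sR = 0.0965
- λ = ln(0.9035/0.614)/48 = 0.00805
- Dropped: p = 1 − exp(−0.4185) = 34.2%; benefit 38.6 − 34.2 = 4.4 points
- Kept: p = 0.9035 × 0.342 = 30.9%; benefit 38.6 − 30.9 = 7.7 points
- Relative to plan: 4.4/24.8 = 18% and 7.7/24.8 = 31% of the planned effect

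**Constant hazard.** The 4-week risk is 1 − 0.614^(4/52) = 3.7%, which is 9.5% of first-year events. Dropped: p = 38.6%, difference 0. Kept: p = 0.963 × 0.386 = 37.2%, difference 1.4 points.

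**Range.** False-positive rates are exact binomial enumerations at 56 per arm, two-sided at 0.05. The first value in each cell is for early-event patients dropped (with 56 retained as an approximation), the second for kept.

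| Share of first-year events in 4 weeks | Spurious benefit, points | Uncorrected chi-squared | Continuity-corrected |
|---|---|---|---|
| Common origin (reference) | 0 | 4.8% | 3.1% |
| 9.5% (constant hazard) | 0 to 1.4 | 4.8 to 5.2% | 3.1 to 3.4% |
| 15% | 1.5 to 3.6 | 5.2 to 6.8% | 3.4 to 4.6% |
| 25% | 4.4 to 7.7 | 7.7 to 13.9% | 5.3 to 10.1% |
| 35% | 7.6 to 11.8 | 13.6 to 26.9% | 9.9 to 21.0% |

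At 4 weeks, shares of 25% and 35% need an early hazard about 3.2 and 5.1 times the later one.

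**If follow-up also ended one year after discharge.** The intervention window would then be only 48 weeks. Even with a constant hazard and early-event patients dropped, p = 1 − 0.614^(48/52) = 36.3%, a spurious benefit of 2.3 points. This is one possible reading of the follow-up statement, not something the article says.

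**The case against.** The case against accepts that the origins differ. It is about size and about what else can be inferred.

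- **The bias may be small.** Both windows are nominally a year long. Under a constant hazard the difference is 0 to 1.4 points and the false-positive rate barely moves. The population includes stable angina, and stable angina is also counted as an event, so strong early concentration of risk cannot be assumed. This stands. A reader might infer that the trial is bound to produce a large false benefit, but nothing in the article establishes that.
- **The gap is inferred.** The article does not date the first session relative to discharge. Three weekly sessions make completion after discharge likely, but the length of the gap is unknown. This stands, and it is why a range is shown.
- **The error rates depend on the test.** The article names both Pearson's chi-squared and Fisher's exact test, and its sample size matches a continuity-corrected calculation. With the correction, the 25% case gives 5.3 to 10.1% against a reference of 3.1%. This stands.
- **The total of one year.** A reader might conclude that this statement makes the intervention window impossible. It does not, because no origin is named and the year could run from each arm's own start. It is an ambiguity that fits awkwardly with the outcome definition.
- **An abstract condenses.** That is true, but an undivided window from discharge is a different definition of the primary outcome, so the contradiction remains.

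None of this removes the unequal origin or gives early deaths in the intervention arm a window.

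**Conclusion.** The point holds and should be corrected before analysis. The primary outcome definition uses arm-specific time zeros, one of them conditional on completing treatment. It contradicts the abstract, and it leaves some randomised intervention patients without a defined outcome.

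The importance rests on the definition itself, not on any one assumed magnitude. Over the scenarios shown, all with no true effect and a 4-week gap, the spurious benefit runs from nil to 11.8 points. The upper half of that range requires markedly front-loaded risk. Where there is a bias in these scenarios, it favours the intervention. The sample size of 56 per group reproduces and is not called into question by this point.

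**What to change.** Define the primary outcome identically in both arms: first major cardiovascular event from randomisation to 12 months after randomisation, in all randomised patients, with events before and during the TPE sessions counted. Randomisation is the better single origin because the article does not say whether it precedes discharge. If it follows discharge, a discharge origin would include time before allocation.

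Bring the abstract, Settings and participants, the Intervention section and Outcomes into line with that origin. Report the year after TPE completion only as a supplementary description.

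The cost is a short amendment. Confirmation from medical records is already planned and can supply event dates, and the sample size stays at 56 per group. The downside is that the result may look less favourable to the intervention than under the present definition.

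### The primary composite counts stable angina, an entry diagnosis, without requiring it to be new, and leaves out unstable angina

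*Protocol article*

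**What the plan says.** The inclusion criteria (Settings and participants) admit acute myocardial infarction with or without ST elevation, together with "patients with unstable angina, and patients with stable angina". The two forms of angina are named separately there.

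The Primary outcome section then sets out the composite: "The primary outcome is based on the occurrence of acute myocardial infarction, stable angina, coronary revascularization, stroke, hospitalized heart failure". Cardiovascular death completes the list. Heart failure carries a qualifier (it must involve hospitalisation). Stable angina carries none. Unstable angina does not appear.

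The counting window is given by arm. For controls it is "the occurrence of major cardiovascular events in the year following hospital discharge for the control group". Patients allocated to the platform are instead counted "in the year following completion of the TPE program with digital follow-up for the intervention group". Events are "systematically obtained through follow-up interview at 12 months and confirmed by reviewing patients’ medical records".

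The Variable definitions section covers the cardiovascular health metrics and the SF-12 scores. It defines no component of the composite. No section says how a condition already present at entry is to be treated.

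**The concern.** Stable angina is a persisting condition, not a dated event. When it is both a reason for entry and an unqualified component of the endpoint, the text gives no rule for the patient who enters with it and still has it at 12 months. Two assessors could score that patient differently and both claim to follow the protocol. Record review does not resolve it, because the record of such a patient will confirm stable angina.

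If these patients are scored, they add events in both arms that say nothing about the intervention. The risk difference moves toward zero and power falls.

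The omission works the other way. An admission for unstable angina in the follow-up year is not an event unless it leads to another listed component, such as infarction, revascularisation or cardiovascular death.

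**Working it through.** **Inputs.** The sample-size paragraph (Settings and participants) assumes an "incidence of a major cardiovascular event of 13.8% in the intervention group and 38.6% in the control group". The same paragraph fixes the error rates in these words: "with a power of 80% and a first-species risk α of 0.05". Its result is 56 per group. The Intervention section gives equal allocation and 112 in total. Sidedness is not stated; I take two-sided. The share f of patients entering with stable angina is not given anywhere, so it is an assumption below.

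**Step 1: reproduce the plan's figure.** With p₁ = 0.386, p₂ = 0.138, mean 0.262 and difference 0.248:

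- n₀ = [1.96 √(2 × 0.262 × 0.738) + 0.8416 √(0.386 × 0.614 + 0.138 × 0.862)]² / 0.248² = (1.2188 + 0.5021)² / 0.0615 = 48.2, so 49 per group without continuity correction.
- With continuity correction, n = (n₀/4) × [1 + √(1 + 4/(n₀ × 0.248))]² = 55.9, so 56 per group.

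The stated 56 is reproduced exactly. The sample-size arithmetic is not at fault.

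**Step 2: effect of counting angina present at entry.** Suppose a share f in each arm enters with stable angina, all of them are counted, having it is unrelated to the other components, and the planned rates apply to the other components only. The observed risk in each arm is then p′ = p + f(1 − p), and the difference becomes 0.248 × (1 − f).

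For f = 10%: control 0.386 + 0.1 × 0.614 = 44.7%; intervention 0.138 + 0.1 × 0.862 = 22.4%; difference 22.3 points. The other rows follow in the same way. Power is for the uncorrected chi-squared test, two-sided 0.05, 56 per arm, by full enumeration of the two binomials.

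| f (assumed) | Control | Intervention | Difference, points | Power |
|---|---|---|---|---|
| 0 | 38.6% | 13.8% | 24.8 | 87% |
| 10% | 44.7% | 22.4% | 22.3 | 72% |
| 20% | 50.9% | 31.0% | 19.8 | 56% |
| 40% | 63.2% | 48.3% | 14.9 | 34% |

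A normal approximation gives 86%, 71%, 57% and 35% for the same rows. By the continuity-corrected formula of step 1, the number per group needed for 80% power would rise from 56 to 78, 106 and 187.

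**Step 3: does another part of the text close the gap?** The window restricts when an event counts, not whether the angina must have begun in it. The 12-month interview and record review establish that a condition exists, not that it is new. No section excludes conditions present at entry.

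**The case against.** The strongest reply is that the outcome is the occurrence, elsewhere the incidence, of major cardiovascular events in a defined year, and that both words ordinarily mean something new. On that reading unchanged baseline angina is no event and the table in the working does not apply. This stands in part: the text does not oblige anyone to count every persisting case. It does not forbid it either, and an unqualified chronic diagnosis beside a qualified one leaves the choice to the assessor.

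A second reply is that *stable* is a misprint for *unstable*. The other components are acute events, procedures or deaths, and one changed word would cure both halves of the problem. That is plausible. However, the inclusion criteria distinguish the two conditions, and the definition rests on a cited source that is not at hand. If it is a slip, the stated primary endpoint is still wrong and needs correcting.

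Third, the power figures rest on an assumed f, on every such patient being counted, and on the planned rates excluding stable angina. The protocol does not say which composite those rates cover. This stands: the table is an illustration, not a forecast.

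Three stronger readings are tempting and are not supported:

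- *Patients meet the endpoint at enrolment.* The window opens at discharge or at completion of the education programme, so nobody scores at the enrolment visit.
- *Daily reporting inflates recorded angina in the intervention arm.* The data listed in the Abstract are compliance, steps, diet and weight, smoking cessation and medication adherence. The support contract's parameters are not specified, and angina symptoms are not mentioned.
- *The 87% at f = 0 contradicts the planned 80%.* It does not. The 56 per group reproduces at 80% with continuity correction, and the exact power of the corrected test at that size is about 81%.

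**Conclusion.** The endpoint as stated is defective and should be corrected before outcome data are reviewed. Two facts carry this without any assumption: stable angina is both an entry diagnosis and an unqualified component of the primary composite, and unstable angina is an entry diagnosis that the composite omits. Whether the wording is intended or a slip cannot be settled from the document, and the need for correction does not depend on it.

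The size of the harm is conditional. If no angina present at entry is counted, there is no dilution. If all of it is counted, the difference falls in proportion to f, and under the assumptions in the working even f = 10% takes uncorrected chi-squared power below the planned 80%. The loss from omitting unstable angina cannot be sized from the document, and is limited to admissions that lead to no other listed component.

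**What to change.** Reconcile the inclusion criteria and the Primary outcome section by an amendment made before any outcome data are reviewed:

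1. Replace stable angina in the composite with unstable angina requiring hospitalisation, or delete it.
2. State that a condition present at randomisation counts only if a new event occurs after follow-up starts.
3. If stable angina is of interest, report new or worsening cases as a separate secondary outcome.

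The cost is a change of wording, with no added visits or data collection. The composite may yield fewer events in total. If the planned rates hold for the corrected composite, 56 per group remains the calculated size.
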